#### Additional analyses

To examine the explanatory mediators, path modelling for mediation analysis will be used. We will test the model at mid- and post- trial with active aging as the primary dependent variable, the intervention condition as the independent variable, and the psychological variables (perceived autonomy support, autonomous motivation, attitudes, subjective norms, perceived behavioral control and intentions) as multiple mediators. Potential trajectories of the outcome and explanatory variables will also be examined. The participant flow diagram during the trial is displayed in Fig. 2.

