Motivation is a psychological concept defined as ‘a driving force for the goal-directed behavior’ [15]. Influencing motivation in counselling interventions is essential, as it underlies the efforts to change behaviors [14]. Autonomous motivation is linked with positive changes, e.g. in physical activity, and refers to engagement based on pleasure or personal importance to the individual rather than extrinsic control, such as fear of punishment [5]. The integration of two socio-cognitive theoretical models, the self-determination theory [5] and the theory of planned behavior [16], is used as the theoretical framework of the AGNES intervention. The Self-Determination Theory (SDT) is a motivation theory and is concerned with supporting our natural or intrinsic tendencies to behave in effective and healthy ways, whereas the Theory of Planned Behavior (TPB) links one’s beliefs and behavior. A previous meta-analysis provided evidence supporting the integration of the two theories [17], and hence their integration is expected to provide complementary explanations of the processes that underlie motivated behavior. Although the SDT framework has been widely used to explore and explain the motivation behind everyday activities in older people [18–20] and the TPB to explain how older individuals intend to behave [21–25], the integrated model has hitherto only been used as a process model in seeking to explain the behavior of older adults [26]. There is a lack of intervention research testing the integrated model’s ability to explain behavior change in older adults across time.

Our view is that increased activity will also increase well-being. While the dictionary definition of well-being is “a good or satisfactory condition of existence”, in empirical research, well-being is often assessed as the absence of specific indicators of ill-being such as depressive symptoms [27]. Increasing participation in various valued social and leisure activities may alleviate depressive symptoms [28]. Positive indicators of well-being include psychological well-being, which is characterized by, for example, a striving to find one’s true nature, personal growth and autonomy, and purpose in life [29]. However, there is less evidence on how to promote positive aspects of well-being. As our goal is to promote activities in line with a person’s goals and values and to support autonomy, it is likely that achieving this goal will also improve psychological well-being.

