### Intervention

The active aging counselling intervention targets several different behaviors that vary between individuals. Consequently, we follow the guidelines of the Medical Research Council (MRC) framework for complex interventions [42] and implementation research [43–45]. A central key aim of the AGNES intervention is to support older individuals’ autonomous motivation in seeking to participate in activities that they personally value. Individuals have a key role in setting their goals, planning their actions and monitoring their progress in change process. Another key issue is the individualization of the counselling sessions (face-to-face and phone calls) after profiling the participants, in order to better meet their needs. Profiling is defined as “the recording and analysis of a person’s psychological and behavioral characteristics, so as to assess or predict their capabilities in a certain sphere or to assist in identifying categories of people” [46]. The profiling sources are participants’ baseline data on the main areas of their everyday life such as health, social contacts, well-being, and preferred activities and goals.

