### Outcomes and measures

Table 2 lists all the measures of the study along with references, the data collection methods and time points.

**Table 2 Tab2:** Measures, data collection time points, methods and references in the AGNES intervention

Assessment / method / scale	Pre-	Mid-	Post-	References
Main outcome				
Active Aging (68 items UJACAS Scale)	HI	HI	HI	[4]
Secondary outcomes				
Psychological well-being (42-item Scale of psychological well-being)	HI	–	HI	[49]
Depressive symptoms (CES-D questionnaire; 20 items)	HI	–	HI	[50]
Quality of life (13-item OPQOL-brief questionnaire)	HI	–	HI	[52]
Personal goals (single item)	PhI	HI	HI	[62]
Life-space mobility (15-item LSA questionnaire)	HI	–	HI	[35]
Walking difficulty	HI	–	HI	[54]
Sense of autonomy outdoor mobility (five-item subscale of IPA)	HI	–	HI	[56]
One-week physical activity surveillance (with tri-axial accelerometers)	HI	–	HI	[58]
Self-reported habitual physical activity (eight-item YAPS)	HI	–	HI	[59]
Theory-based explanatory measures				
Perceived autonomy support (five items)	PhI	HI	HI	[63]
Autonomous-controlled motivation (eight items)	PhI	HI	HI	[64]
Attitude towards active aging (three items); Subjective norms of active aging (single item); Perceived behavioral control over active aging (single item); Intention for active aging (single item)	PhI	HI	HI	[65]
Descriptive measures				
Education (single item) & Perceived financial situation (single item)	HI	–	–	[66]
Physical health	HI	–	–	[67]
Lower extremity physical performance (SPPB)	HI	–	–	[69]
Maximal isometric handgrip strength (hand-held dynamometer)	HI	–	–	[71]
Cognitive functioning (19-item MMSE)	HI	–	–	[41]
Changes in life situation (five items)	PhI	HI	HI	–
Habitation (single item)	HI	–	–	–
Self-rated health (single item)	HI	–	–	[72]
Perceived age (single item)	HI	–	–	[73]
Perceived active aging (single item)	HI	–	–	[4]
Motivation for active aging (single item)	HI	–	–	[4]
Feeling of loneliness (single item)	PQ	–	–	[74]
Social contacts (three items)	PQ	–	–	[67]
Current hobbies (single item)	HI	HI	HI	–
Assessment debriefing (one item)	HI, PhI	HI	HI	–
Intervention debriefing (one item)	–	–	HI	–

For each assessment, according to the time point (pre, mid and post), the method of data collection is indicated as Home Interview (HI), Postal Questionnaire (PQ) or Phone Interview (PhI)

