### Theory-based explanatory measures

Additional explanatory data will be collected at baseline, mid- and post-trial, from both groups.

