#### Autonomous-controlled motivation

The Self-Regulation Questionnaire [64] adapted to meet the needs of the intervention, is used to assess individual differences in the types of motivational regulation for being more active. The questionnaire consists of two sub-scales: autonomous motivation (4 items: e.g., “Because I enjoy being an active person”) and controlled motivation (4 items: e.g., “I would feel like a failure if I do not live an active life”). Answers are given on a Likert-type scale ranging from: 1 = “strongly disagree” to 7 = “strongly agree”. The participant’s score for each subscale is the mean score for the 4 items.

The constructs pertaining to the theory of planned behavior have been developed following the recommendations given in the manual for health services researchers [65] for the needs of the present study. *Attitude* towards being more active is assessed with 3 items scored on 7-point semantic differential scales ranging from 1 to 7 (“Aiming to live a more active life during the next six months means to me … pleasant - unpleasant, difficult - easy, useful - useless”). *Subjective norms of active aging* are assessed with one item: “I feel that the people who are important to me would want/expect me to live a more active life for the next six months”. Responses are given on a 7-point scale ranging from 1 = “strongly disagree” to 7 = “strongly agree”. *Perceived behavioral control over active aging* is assessed with one item: “I am confident that I can live a more active life for the next 6 months”. Responses are given on a 7-point scale ranging from 1 = “strongly disagree” to 7 = “strongly agree”. *Intention for active aging* is assessed using one item: “I intend to live a more active life for the next 6 months”. Responses are given on a 7-point scale ranging from: 1 = “strongly disagree” to 7 = “strongly agree”.

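### Controlled motivation is scored at all three visits but left out of the listed mediators, so the autonomous-motivation path can be biased in either direction

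*Protocol article*

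**What the plan says.** The Aims section of the protocol article includes an examination of mechanisms related to active aging. The Background describes autonomous motivation as "engagement based on pleasure or personal importance to the individual rather than extrinsic control", and the Intervention section states: "A central key aim of the AGNES intervention is to support older individuals’ autonomous motivation".

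The measurement plan covers both sides of that description:

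- Under Autonomous-controlled motivation: "The questionnaire consists of two sub-scales: autonomous motivation" with four items, and controlled motivation with four items. The participant's "score for each subscale is the mean score for the 4 items", so each subscale has its own score.
- Table 2 has a row "Autonomous-controlled motivation (eight items" with entries at pre-, mid- and post-trial.
- Under Theory-based explanatory measures: "Additional explanatory data will be collected at baseline, mid- and post-trial, from both groups".

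Additional analyses then sets out a path model with intervention arm as the independent variable, active aging as the dependent variable, and as multiple mediators the "psychological variables (perceived autonomy support, autonomous motivation, attitudes, subjective norms, perceived behavioral control and intentions". The list is closed, with no wording to mark the six as examples. Controlled motivation is the only scored explanatory construct not on it. The same section adds, without a method, that trajectories of the outcome and explanatory variables may be examined.

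**The concern.** The mediation model is meant to show whether counselling works by way of autonomous motivation. The protocol describes that construct by contrast with extrinsic control and measures both, yet the model contains only one of them. A person's autonomous and controlled scores come from the same questionnaire at the same visit and may well be correlated. If controlled motivation also affects active aging, leaving it out makes it an omitted common correlate of the mediator and the outcome. Randomisation protects the arm effect on each mediator, but not the mediator-outcome coefficient.

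At stake is the reading of the mechanism result. A reported autonomous path could be partly or wholly borrowed from controlled motivation, or a real one could be understated.

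**Working it through.** **Inputs from the protocol.** Two separately scored subscales at three visits in both arms; six named mediators, of which controlled motivation is not one; 200 participants with 20% attrition allowed for (200 × 0.8 = 160 remaining). The protocol gives no figure for the mediation analysis, so there is none to reproduce. The arm effects on the subscales, their correlation and their effects on active aging are not stated, and every value for them below is an assumption.

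**Model.** With T the arm, M1 autonomous and M2 controlled motivation, and unit residual variances:

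- M1 = a1·T + e1
- M2 = a2·T + e2, with corr(e1, e2) = rho
- Y = c·T + b1·M1 + b2·M2 + error

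Write e2 = rho·e1 + u. Then M2 = a2·T + rho·(M1 − a1·T) + u. Substituting for the omitted M2 gives:

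- estimated autonomous path = a1·(b1 + rho·b2), so its error is a1·rho·b2
- estimated direct effect = c + b2·(a2 − rho·a1)

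The arm effect on controlled motivation, a2, appears only in the direct effect.

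**Large-sample check** (400,000 simulated participants; a1 = 0.4, c = 0; a2 = 0.3 unless shown):

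| b1 | b2 | rho | True path a1·b1 | Formula, M2 omitted | Simulated, M2 omitted |
|---|---|---|---|---|---|
| 0.3 | 0.3 | 0.3 | 0.12 | 0.4 × 0.39 = 0.156 | 0.156 |
| 0.3 | 0.3 (a2 = 0) | 0.3 | 0.12 | 0.156 | 0.158 |
| 0.3 | −0.3 | 0.3 | 0.12 | 0.4 × 0.21 = 0.084 | 0.086 |
| 0.3 | −0.3 | 0.6 | 0.12 | 0.4 × 0.12 = 0.048 | 0.047 |
| 0.3 | 0.3 | −0.3 | 0.12 | 0.4 × 0.21 = 0.084 | 0.083 |
| 0.3 | 0.3 | 0 | 0.12 | 0.12 | 0.119 |
| 0 | 0.3 | 0.3 | 0 | 0.4 × 0.09 = 0.036 | 0.035 |

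In the first two rows, changing a2 from 0.3 to 0 leaves the autonomous path essentially unchanged. The direct effect moves from 0.3 × (0.3 − 0.12) = 0.054 to 0.3 × (0 − 0.12) = −0.036 (simulated 0.049 and −0.037).

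**At trial size** (180 participants, a value between 160 and 200; 3,000 replicates; the path is called significant when both of its legs are). With a1 = 0.5, b1 = 0 and b2 = 0.3, any autonomous path is false:

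| rho | Mean false path, 0.5 × rho × 0.3 | Significant, M2 omitted | Significant, M2 included |
|---|---|---|---|
| −0.2 | −0.030 | 10-11% | 4-5% |
| 0 | 0 | about 5% | 4-5% |
| 0.2 | 0.030 | 10-11% | 4-5% |
| 0.4 | 0.060 | 30-32% | 4-5% |
| 0.5 | 0.075 | 43% | 4-5% |

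At rho = 0.4 the rate is about 30% with no arm effect on controlled motivation and about 32% with a rise of 0.4 SD. The simulation error at 30% is √(0.3 × 0.7 / 3,000), or 0.8 percentage points.

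**Masking case.** With a1 = 0.5, b1 = 0.3, b2 = −0.3 and rho = 0.4, the path falls from 0.5 × 0.3 = 0.150 to 0.5 × (0.3 − 0.12) = 0.090. Detection falls from 87% to about 57%.

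**The case against.** **The list follows the hypothesis.** The stated hypothesis is about supporting autonomous motivation, and restricting the mediators to the hypothesised pathway is a legitimate choice. The protocol nowhere promises a test of autonomous against controlled motivation. This stands, and a reader should not infer that a promised contrast has been dropped. But the choice of pathway does not remove the bias in that pathway's own estimate.

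**The size depends on assumptions.** With rho = 0 or b2 = 0 there is no bias. With b2 = 0.1 at rho = 0.4 the false-path rate is only about 8%. The illustration also leaves out the other five planned mediators. Subjective norms concern what important others want, and perceived autonomy support runs from supportive to controlling, so both may carry part of the same information. Adding one such covariate, with assumed correlations of 0.3 with autonomous and 0.5 with controlled motivation, cut the 32.5% rate obtained in that run to 15%. This stands too: the percentages show what is possible and do not forecast this trial. The controlled item the protocol quotes is about feeling like a failure, which is internal pressure, so a norms item is at best a partial substitute.

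**Counselling pressure.** A reader might infer that repeated follow-up raises felt pressure and that the model credits this rise to autonomous motivation. The documents give no ground for assuming such a rise, and in a parallel-mediator model it would enter the direct effect. It reaches the autonomous path only if controlled motivation also drives autonomous motivation, and then only slightly in the case tried (path 0.035 with controlled motivation omitted against 0.027 with it included, for a1 = 0, a2 = 0.3 and an effect of 0.3 of controlled on autonomous motivation).

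**Nothing need go unseen.** A reader might also infer that a rise in pressure would stay hidden. The planned trajectories of explanatory variables can include controlled motivation. They would show it over time, but would neither test its mediating role nor remove the bias.

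**Conclusion.** The point holds as a minor one. The article scores controlled motivation separately at every visit in both arms, closes the mediator list without it, and gives no reason. As written, the model cannot separate the autonomous path from whatever controlled motivation shares with it. The error is a1·rho·b2: it can inflate, shrink or create the path, and it vanishes if the subscales are uncorrelated or controlled motivation has no effect on active aging.

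Under the assumed values, the chance of a false significant path runs from the nominal level at zero correlation to 43% at 0.5. These figures rest on linear effects, two mediators only, and parameter values that the documents do not supply. The point concerns an additional analysis. The primary effect estimate and the sample size are untouched.

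**What to change.** In Additional analyses, add controlled motivation to the mediator list at the same visits as autonomous motivation, and leave the residual correlation between the two free. Report the arm difference on both subscales, which shows directly whether counselling changes controlled motivation. If the subscale is left out on purpose, give the reason before the data are analysed, so that the set of mediators is not a post-hoc choice.

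The cost is one more mediator from data already being collected. In the two-mediator illustration, the standard error of the autonomous-motivation coefficient changed by about −4% to +12%, so intervals widen slightly where the subscales are clearly correlated.

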**Fig. 2 Fig2:**
[figure not shown]
Participant flow diagram in the AGNES intervention

### Data management and data reporting

The University of Jyväskylä has full ownership of the research data. Consent forms and paper questionnaires will be stored in locked cabinets in a project researcher’s office. Computer assisted interviewing techniques are used, whenever possible. Digital data will be stored on computer drives of the Information Management Center of the University of Jyväskylä. All datasets will be pseudonymized. Data will be managed by AGNES research team members appointed for this task. The key for participant identification will be stored separately from the data files and only accessible to designated research team members. Research team members can use pseudonymized datasets for research and teaching purposes, providing they are employed by the University of Jyväskylä. Results will mainly be reported in articles published in established international scientific journals and presentations in scientific and professional congresses. The researchers will target open access publishing and comply with the University of Jyvaskyla recommendation for parallel publishing in the open access digital JYX repository. Results will be communicated at events and in meetings and through traditional and social media for professionals and the general public.

## Discussion

The AGNES intervention study will provide new knowledge on the effects of individualized counselling on active aging. We will test the idea that supporting autonomous motivation to engage in personally important preferred activities will increase participation in these activities, and eventually also improve different aspects of well-being. Novel features of the AGNES intervention trial include the theory-based counselling intervention and the outcome of active aging, which is quantifiably assessed with a recently launched measure [4].

The idea for the intervention stems from our earlier observational studies and randomized controlled trials. As we have reported previously [76], personal goals correlate with life-space mobility, a variable which indicates the extent to which a person participates in different activities outside the home. Our earlier randomized controlled trial on the effects of physical activity counselling bears similarities with the present study in counselling approach used [77]. The trial proved efficacious in increasing physical activity [78]. Since conducting these studies, additional evidence has accumulated suggesting that any activity outside the home will have benefits induced, e.g., by increased physical activity and more social interaction with others; see, e.g., [8, 9]. We have therefore expanded the scope of the intervention to promote any self-selected activity and refined the counselling approach based on new knowledge on behavior change techniques.

The present study will produce new knowledge on the potential of older people to promote their own well-being. We aim to update knowledge on the positive aspects of aging and activity in older age. We also expect further knowledge and theory on successful counselling methods.

We are currently recruiting participants for the AGNES intervention study from the population-based AGNES cohort study [39], which uses probability sampling. This will likely help us avoid some of the biases characteristic of convenience sampling, i.e., that participants represent individuals who are the most interested in the study topic. We are starting by excluding the most active volunteers in order to recruit participants who have room for improvement. We are also excluding those whose life-space mobility is very low, as it is likely that they experience many barriers to increasing activity on their own initiative and would probably benefit from a more intensive intervention. We are following the guidelines for planning and conducting randomized trials. The research group meets regularly to discuss the progress of the study. The counsellor delivering the intervention has a support system and the counselling sessions are periodically monitored.

The study site is a medium-sized Finnish city (population 139.260) that is age-friendly and provides many activity opportunities for older people. It is likely that different living environments need different study approaches. For example, rural areas and big cities present different opportunities and challenges for participation. Although the intervention will be delivered to all participants assigned to it by a highly motivated and well-trained professional counsellor, the intervention may nonetheless be considered a trial in a real world setting in the sense that the population is community-based and rather heterogeneous, which in turn means that variation in compliance is inevitable.

## Abbreviations

AAI: Active Aging Index
BCT: Behavior Change Techniques
CES-D: Centre for Epidemiologic studies Depression Scale
CG: Counselling group
FIML: Full information maximum likelihood
HI: Home interview
HIG: Health information group
IPA: Impact on Participation and Autonomy questionnaire
LSA: University of Alabama at Birmingham Study of Aging Life-Space Assessment
MAR: Missing at random
MMSE: Mini-Mental State Examination
OPQOL: Older People’s Quality of Life questionnaire
PhI: Phone interview
PQ: Postal questionnaire
SDT: Self-Determination Theory
SPPB: Short Physical Performance Battery
TPB: Theory of Planned Behavior
UJACAS: University of Jyvaskyla Active Aging Scale
